##### Methods to handle missing data

In principle, the rate of missing data is estimated to be very low due to the type of endpoint, easily available with a fast-clinical assessment, so no impact on the primary analysis is expected. In any case, a very conservative strategy will be implemented consisting of imputing any missing data or other binary efficacy secondary outcomes will be considered to failures, irrespectively to the reason for missingness. With regard to the continuous variables, mixed models [9–11] are robust to the presence of missing at random (MAR) and conduct the analysis with all participants despite the presence of missingness. Of note, this method calculates the estimations based on the variance-covariance structure but without any formal imputations.

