### Sample size

We propose an open-label, standard of care controlled, randomized (1:1 ratio) clinical trial with stopping boundaries for efficacy and futility at 20, 40, 60, and 80% of the final sample size. The statistical design including the sample size and stopping have been calculated using the East validated software v6.5 by Cytel Inc. The stopping boundaries for superiority and inferiority have been calculated using the rho family spending functions.

The primary outcome measure is the proportion of patients that progress to category 5, 6, or 7 (hospitalized with severe disease or death categories of the 7-point ordinal scale), at day 15. With this design, 278 patients (139 per arm) will be required assuming 20% rate in the control group and an absolute reduction of 10% (10% rate in experimental group), with 80% statistical power and a 2.5% one-sided alpha level (5% two-sided). Likewise, approximately 140–200 CP donors will be needed.

With regard to the final sample size, it is predefined that a sample size recalculation will be put in place when 60% of the patients with assessed events at day 15 are available and the 3rd analyses are conducted.

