### Assignment of interventions: blinding

This is an open-label study. To reduce treatment bias, the eCRF did not allow randomizing a subject until sufficient clinical information from the subject was already included, reducing the possibility that a given subject could be re-randomized. Additional measures were implemented to reduce assessment bias, e.g., clinical information was collected, and daily clinical decisions were taken by the medical staff at each study center, that in most cases were not part of the research team. The primary endpoint was restricted to WHO scores ≥ 5 in an attempt to not only focus on relevant outcomes, but also to increase the robustness of the endpoint; although some scores are subjected to clinical judgment, these are hardly influenced by the clinical trial participation and/or treatment assignment.

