### Data collection and management

#### Plans for assessment and collections of outcomes

Investigators are responsible for assessment and collection of outcomes, baseline, and other trial data. Data will be entered in the CRF by delegated team members and will be monitored by the clinical research associated. Subjects will be assessed daily while hospitalized. Patients discharged before the end of follow-up will be regularly phoned or asked to attend study visits. NP/OP swabs for virus analysis and blood samples for serological analysis will be sent to a central laboratory, where test will be performed according to laboratory standard operating procedures.

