### Trial status

Patient’s recruitment started on 4 April 2020, under conPlas-19 Protocol version 2.2 as of 22 April 2020. Donor’s recruitment started on 2 April 2020. As of 10 July 2020, patients’ recruitment was temporarily interrupted awaiting some study modifications. By 31 August, the study design was amended to restrict the inclusion to patients with no more than 7 days of symptoms, and the follow-up was extended up to 60 days. ConPlas-19 Protocol version 3.3 as of 30 September 2020 is now in place, allowing the use of rapid antigenic tests as laboratory confirmation test for SARS-CoV-2 infection.. It is anticipated that recruitment will be complete by end of 2020.

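### Counting every missing binary outcome as a failure is called very conservative, but it favours plasma if controls are missing more often, and read literally it scores survivors without a day-60 status as dead

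*Protocol article*

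**What the plan says.** Under Methods to handle missing data, the protocol article first sets an expectation: "In principle, the rate of missing data is estimated to be very low due to the type of endpoint". It then fixes a rule: "a very conservative strategy will be implemented consisting of imputing any missing data or other binary efficacy secondary outcomes will be considered to failures", and this applies "irrespectively to the reason for missingness". The sentence is garbled. It follows directly on a statement about the primary analysis, so the natural reading is that it covers both the day-15 primary endpoint and the binary secondary efficacy outcomes.

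Four other places bear on it:

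- **Blinding:** "This is an open-label study".
- **Collection of outcomes:** "Patients discharged before the end of follow-up will be regularly phoned or asked to attend study visits". Day-15 status after discharge therefore depends on contact with the patient.
- **Follow-up:** the Abstract (Methods/design) gives 30 days. Trial status says recruitment began on 4 April 2020 and was interrupted on 10 July, and that by 31 August "the follow-up was extended up to 60 days".
- **Secondary outcome measures:** all-cause mortality at day 60 is listed, separately from the safety item. Statistical methods adds that binary efficacy and safety outcomes are analysed in the same way as the primary endpoint.

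**The concern.** Two separate problems follow from one sentence.

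**Direction.** Scoring missing as failure raises the failure rate in whichever arm has more missing data. If that arm is plasma, the rule works against plasma. If it is control, the rule works for plasma. The label promises the first and the design does not guarantee it. In an open-label add-on trial, missingness can differ by arm. A false-positive primary result could then be presented as having survived a conservative analysis.

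**Day 60.** The rule makes no exception for an assessment that was not in a patient's schedule at entry. Some patients entered while the planned follow-up was 30 days. Read literally, a patient alive at day 30 with no later contact counts as a death at day 60. The recorded mortality would then reflect the amendment date as well as the disease.

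**Working it through.** **Inputs from the article (Sample size).** Failure rates of 20% on control and 10% on plasma, a one-sided test at 2.5%, a target power of 80%, and 139 patients per arm. No missing-data rate is given, so every missing rate below is an assumption.

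**The plan's own figure.** The standard fixed-sample formula for 20% against 10% gives 199 per arm, not 139. Power at 139 per arm is about 65%. That is a separate matter. I use 139 per arm only because it is the stated size, and nothing below depends on how it was derived.

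**Step 1: effect of the rule on the observed rate.** Let the true failure rate be p, the missing fraction m, and let missing patients have the same underlying rate as the others. Then

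observed rate = m + (1 − m) × p.

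For p = 0.20 and m = 0.05: 0.05 + 0.95 × 0.20 = 0.24.

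**Step 2: chance of a significant result for plasma when there is no effect.** Exact binomial probabilities, 139 per arm, single-look one-sided pooled z-test at 1.96, true rate 20% in both arms:

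| Missing, control / plasma | Observed, control / plasma | One-sided error |
|---|---|---|
| 0% / 0% | 20.0% / 20.0% | 2.5% |
| 2% / 0% | 21.6% / 20.0% | 5.1% |
| 5% / 2% | 24.0% / 21.6% | 6.8% |
| 5% / 0% | 24.0% / 20.0% | 12.3% |
| 5% / 5% | 24.0% / 24.0% | 2.5% |
| 0% / 5% | 20.0% / 24.0% | 0.3% |

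**Step 3: the same in patient counts.** With 28 control and 20 plasma failures, z = 1.27. Five missing controls (5/139 = 3.6%) scored as failures give 33 against 20 and z = 1.98, above 1.96.

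**Step 4: day-60 mortality.** Let f be the share of patients with no day-60 status and q the true mortality. Applying the rule literally,

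recorded mortality = f + (1 − f) × q.

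With q = 10%: f = 10% gives 0.10 + 0.90 × 0.10 = 19%, and f = 50% gives 0.50 + 0.50 × 0.10 = 55%. Randomisation is 1:1 throughout, so f should be about equal in the two arms. If true mortality were 10% on control and 5% on plasma (risk ratio 0.50):

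| f (assumed) | Recorded, control / plasma | Risk ratio |
|---|---|---|
| 10% | 19.0% / 14.5% | 0.76 |
| 25% | 32.5% / 28.8% | 0.88 |
| 50% | 55.0% / 52.5% | 0.95 |

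**Step 5: dates.** Counting 60 days back from 31 August 2020 gives 2 July. Patients enrolled from 4 April to about 2 July had passed day 60 by the date given for the amendment. Those enrolled from then until the pause on 10 July reached it afterwards. The article does not say how many there were, or whether vital status was obtained later.

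**The case against.** The best defence is that missingness will be negligible. The endpoint is at day 15, treatment is a single infusion, inpatients are assessed daily, discharged patients are contacted, and patients are to be followed whenever possible regardless of adherence. The 12.3% figure needs about 7 of 139 controls missing and no plasma patient missing. Nothing in the article points to such an imbalance. This stands: the article shows that the label is not assured, and a reader who infers that the primary result will be biased towards plasma goes beyond it. Nor does it say that the patients who are missing will mostly be those discharged well, plausible as that is.

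A reader might also count the loss of power under equal missingness as a fault. With 5% missing in each arm, 20% against 10% becomes 24% against 14.5%. That attenuation is what a conservative rule does, so it is not part of this point.

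On day 60, a reader might conclude that mortality will be wrong by tens of percentage points. The article does not support that unconditionally. Later collection of vital status is not excluded, the affected share is not given, and at f = 10% the inflation is 9 points. It is also arguable whether an assessment never scheduled is missing data at all. The error falls on both arms alike and dilutes the comparison, so it does not favour plasma. Statistical methods already plans Kaplan-Meier and Cox analyses for overall survival, although it does not say that these replace the listed mortality rates.

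Finally, sensitivity analyses may sit in the SAP, which is not shown, and multiple imputation as the primary method would be a matter of choice. Neither absence is a fault here.

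**Conclusion.** The point holds in a limited form and is of moderate severity.

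The rule is stated in the article, not left open, and its description is wrong as a general claim. It is conservative for the treatment comparison only when plasma patients are missing at least as often as controls. Under the assumptions in the working, a 2-point excess of missing controls doubles the one-sided error to 5.1%, and a 5-point excess takes it to 12.3%. Equal missingness leaves it at 2.5%, and an excess on plasma lowers it. The direction cannot be predicted from the article.

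For day-60 mortality, the literal rule turns survivors without a day-60 status into deaths. Recorded mortality of 19% to 55% against a true 10% rests on an assumed 10% to 50% of patients without that status, and on reading the rule as reaching unscheduled assessments. The wording allows that reading but does not compel it, so the article should rule it out.

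**What to change.** 1. Delete the words very conservative, or state the condition: plasma patients missing at least as often as controls.
2. For the day-15 endpoint, use known discharge and vital status to day 15 first, and impute failure only where the outcome remains unknown. Report the number missing by arm.
3. Show the primary result with the assumed outcomes of missing patients varied separately in the two arms, if the SAP does not already do so.
4. State that missing = failure does not apply to an assessment that was never scheduled for the patient.
5. Analyse day-60 mortality by Kaplan-Meier with censoring at last contact, in line with the planned overall-survival analysis, or only in patients enrolled under 60-day follow-up. State whether later vital status was collected for the earlier patients.
6. Repair the garbled sentence so that the outcomes it covers are clear.

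The cost is a few sentences and a small amount of extra analysis. No new data are needed.

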##### Plans to give access to the full protocol, participant-level data, and statistical code

These plans are not yet in place.

#### Trial monitoring

The Spanish Clinical Research Network (SCReN) is responsible for project management, regulatory compliance and trial monitoring.

#### Data management team

PIVOTAL is the CRO responsible for data management, preparation of the eCRD, quality assurance, and preparation of the SAP.

### Composition of the data monitoring committee, its role and reporting structure

The independent DSMB in this study is responsible for reviewing the reports regarding the safety and efficacy of the study patients protocol adherence and making recommendations to continue or terminate the study or to modify the sample size of the basis of the results from the interim analysis. The DSMB members are all independent of the sponsor and have no financial or other conflict of interest.

### Adverse event reporting

Serious adverse events (SAEs) and grade 3 or 4 adverse events will be collected from the time of informed consent to day 29. SAEs will be followed up until the SAE has subsided, returned to baseline, or is stable. Infusion-related adverse reactions will be recorded within 24 h after the end of plasma administration by a trained Hemovigilance nurse or physician, according to the Active 24 h quarantine Hemovigilance Program (HEMACUA).

Investigators will be instructed to actively monitor the occurrence of prespecified adverse events of special interest: TRALI (transfusion-related acute lung injury), ADE (antibody-dependent enhancement of infection, and TACO (transfusion-associated cardiac overload).

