**Methods/design:**

The ConPlas-19 study is a multicenter, randomized, open-label controlled trial. The study has been planned to include 278 adult patients hospitalized with severe COVID-19 infection not requiring mechanical ventilation (invasive or non-invasive). Subjects are randomly assigned in a 1:1 ratio (139 per treatment arm), stratified by center, to receive intravenously administered CP (single infusion) plus SOC or SOC alone, and are to be followed for 30 days. The primary endpoint of the study is the proportion of patients that progress to category 5, 6, or 7 (on the 7-point ordinal scale proposed by the WHO) at day 15. Interim analyses for efficacy and/or futility will be conducted once 20%, 40%, and 60% of the planned sample size are enrolled and complete D15 assessment.

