#### Secondary outcome measures

The secondary outcome measures include the following:

-Ordinal scale (see 7-point ordinal scale above):
Status at day 30Time to category 5, 6, or 7 of the ordinal scale.Time to an improvement of one category from admission on the ordinal scale.Time to first deteriorationMean change in the ranking on an ordinal scale from baseline to days 3, 5, 8, 11, 15, 29, and 60.

-Ordinal scale of 11 points (Additional file 2):
Mean change in the ranking on an ordinal scale from baseline to days 3, 5, 8, 11, 15, 29, and 60Status at day 15 and 30Mortality rate (all cause) at day 15, at day 29, and at day 60.Oxygenation-free days in the first 28 days (day 29).Ventilator-free days in the first 28 days (day 29).Duration of hospitalization (days).Incidence of thrombotic arterial events.Incidence of thrombotic venous events.Rate of rehospitalizations.Serum level of CRP, lymphocyte count, LDH, D Dimer, IL-6, coagulation tests at baseline and at days 3, 5, 8, 11, 15, 29, and 60.Safety assessments of CP + SOC as compared to SOC alone through day 60 considering cumulative incidence of serious adverse events (SAEs), cumulative incidence of Grade 3 and 4 adverse events (AEs), and infusion-related adverse reactions.

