### Statistical methods

#### Statistical methods for primary and secondary outcomes

A detailed Statistical Analysis Plan (SAP) agreed upon by the CT Executive Board and the Project Statistician will be available early during the recruitment phase. This SAP will follow the general regulatory recommendations given in the ICHE9 (CPMP/ICH /363/96) guidance, as well as other specific guidance on methodological and statistical issues [8].

Likewise, it will stick to the recommendations given by the consensus documents of the scientific journals to improve reliability and value of medical research literature by promoting transparent and accurate reporting of clinical research studies.

The proportion of patients with failure, defined as category 5, 6, or 7 of the 7-point ordinal scale at day 15, will be estimated using a log-binomial regression model including stratification variables. In the unexpected event that the model does not fit, the Poisson regression model with long-link and robust variance estimator will be used instead.

Binary efficacy and safety outcomes will be analyzed as described for the primary endpoint.

Kaplan-Meier model will be used to analyze survival endpoints (TTF and OS). In all these analyses, in addition to the Kaplan-Meier curve, median, Q1, Q3, and their corresponding 95% CI, number of events, and censored case distribution will be shown. Group comparisons will be done using the (stratified) log-rank test and the (stratified) hazard ratios (HR) (95%CI) from the Cox model.

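### The safety outcome runs to day 60, but SAEs and grade 3–4 adverse events are collected only to day 29, so non-fatal events on days 30–60 have no stated data source

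*Protocol article*

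**What the plan says.** Under Secondary outcome measures, the protocol article lists "Safety assessments of CP + SOC as compared to SOC alone through day 60 considering cumulative incidence of serious adverse events (SAEs"), then "cumulative incidence of Grade 3 and 4 adverse events (AEs), and infusion-related adverse reactions". The horizon for this between-arm comparison is day 60.

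Under Adverse event reporting, the collection rule is: "Serious adverse events (SAEs) and grade 3 or 4 adverse events will be collected from the time of informed consent to day 29". Two further rules follow. For events already recorded, "SAEs will be followed up until the SAE has subsided, returned to baseline, or is stable". For transfusion reactions, "Infusion-related adverse reactions will be recorded within 24 h after the end of plasma administration".

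Overall follow-up is stated twice. The abstract (Methods/design) says that patients are randomised "and are to be followed for 30 days". Trial status says that, with the 31 August change to the design, "the follow-up was extended up to 60 days".

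On analysis, the statistical methods section says "Binary efficacy and safety outcomes will be analyzed as described for the primary endpoint" and leaves the detail to a statistical analysis plan that is not shown.

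**The concern.** An outcome can be estimated only over the period in which its events are recorded. Here the outcome and the collection rule concern the same two event types, and the rule stops about halfway through the outcome's horizon. A site that follows the adverse event section would stop recording new SAEs and grade 3–4 events at day 29. The analysis would then have nothing to draw on for the remainder.

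Safety is half of the trial's stated objective, and these two incidences are its main between-arm safety measures. If the mismatch stays, a result reported as day 60 would be either a day-29 result with the wrong label or, if some sites continue recording, a blend of observation periods. Unrecorded adverse events are hard to reconstruct later, and the article describes recruitment as still open, so the point was time-sensitive.

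**Working it through.** There is no stated figure to reproduce. The check sets the outcome beside the collection rule, component by component.

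| Component | Outcome horizon (Secondary outcome measures) | Collection (Adverse event reporting, unless noted) | Match? |
|---|---|---|---|
| SAEs | through day 60 | consent to day 29 | No |
| Grade 3–4 AEs | through day 60 | consent to day 29 | No |
| Infusion-related reactions | through day 60 | within 24 h of end of infusion | Yes; these events belong to that window |
| All-cause mortality (separate outcome) | days 15, 29 and 60 | its own assessment days, under Secondary outcome measures | Yes |

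**Step 1: size of the gap.** Outcome horizon: 60 days. Last day of collection: day 29. Uncollected: 60 − 29 = 31 days (days 30 to 60). Share of horizon: 31/60 = 0.517, or 52%. This is a share of calendar days. The article gives no timing of events, so the share of events missed is unknown.

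**Step 2: does another rule fill the gap?** The rule on following SAEs to resolution concerns events already recorded and does not provide for recording new ones. The day-60 mortality outcome captures late deaths. Nothing else shown provides for recording new non-fatal SAEs or grade 3–4 events after day 29.

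**Step 3: can follow-up differ between enrolment periods?** The dates come from Trial status: recruitment from 4 April 2020, interrupted as of 10 July, amended 31 August. The plasma is given on day 1 (Implementation). I assume that randomisation falls on day 1 and that no patient was randomised between the interruption and the amendment.

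- Latest pre-pause patient, day 1 = 10 July: day 30 = 10 July + 29 days = 8 August.
- Same patient: day 60 = 10 July + 59 days = 7 September.
- Patient whose day 60 falls on 31 August: day 1 = 31 August − 59 days = 3 July.

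On these assumptions, every pre-pause patient had passed day 30 before the amendment, and anyone randomised before 3 July had already passed day 60. If 30 days was the follow-up in force for them, days 31–60 were largely or wholly over before the extension. The article does not say whether these patients were re-contacted, nor how many there were.

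**The case against.** The strongest reply is that this is a wording conflict in a condensed article about a secondary outcome. The full protocol and the schedule of procedures are not shown, and the collection window under extended follow-up may be correct there. The collection rule is the same in both arms, so a day-29 comparison is valid and the cut-off favours neither arm. The intervention is a single infusion on day 1, and the primary endpoint at day 15 is untouched.

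Much of this stands. It limits the point to what the article states, and it rules out a claim that the between-arm difference is biased in a known direction. It does not remove the conflict: this is not a detail left to another document, because the article states both windows and they disagree.

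A reader might infer several stronger things that the article does not support:

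- *The whole safety outcome cannot be produced.* Infusion reactions and deaths to day 60 remain available.
- *Late thrombotic events and rehospitalisations will be lost.* These are separate secondary outcomes, and the day-29 rule does not set their window.
- *Uncollected time will be counted as event-free.* The article says only that binary safety outcomes follow the primary model. It does not say that day-60 cumulative incidence is handled that way.
- *The day-29 rule was overlooked when follow-up was extended.* This is plausible, but nowhere stated.
- *Patients enrolled before the amendment cannot contribute after day 30.* The dates make prospective collection unlikely for most of that period, but the article does not rule out later contact.

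**Conclusion.** The contradiction is real and lies in current text. As the article is written, the cumulative incidence of SAEs and of grade 3–4 adverse events can be estimated to day 29 but not to day 60, because non-fatal events with onset on days 30–60 (31 of 60 days) have no stated source. The effect on the between-arm difference is unknown, since the gap applies equally to both arms and no event timing is given.

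The conclusion rests on reading the adverse event section as the operative collection rule. That follow-up may differ by enrolment period is supported by the article's two statements of its length and by its dates. The extent of the difference cannot be determined, because the split of patients is not given.

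**What to change.** Reconcile the abstract, Secondary outcome measures, Adverse event reporting and Trial status. Either route resolves the conflict:

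1. Align the collection window for SAEs and grade 3–4 events with the day-60 outcome for patients under extended follow-up; or
2. Restate the safety outcome for the window in which these events are actually collected.

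Under either route, use day 29 as the common window for the safety comparison in all patients. Report any day-60 cumulative incidence only by a method that censors each patient at the end of that patient's event collection. State the length of follow-up that applied before and after the amendment.

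The first route adds a small collection burden, since day-60 assessments already exist for mortality, the ordinal scales and laboratory values. It cannot recover events that have already gone unrecorded. The second adds no collection burden but shortens the stated safety horizon.
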